## Abstract

**Background:**

Multi-sensory behavioral interventions for preterm infants have the potential to accelerate feeding, growth, and optimize developmental trajectories and increase parents’ interactive engagement with their infants. However, few neonatal intensive care units (NICUs) provide evidence-based standardized early behavioral interventions as routine care. Lack of implementation is a major gap between research and clinical practice. H-HOPE, is a standardized behavioral intervention with an infant- directed component (Massage+) and a parent-directed component (four participatory guidance sessions that focus on preterm infants’ behaviors and appropriate responses). H-HOPE has well documented efficacy. The purpose of this implementation study is to establish H-HOPE as the standard of care in 5 NICUs.

**Methods:**

The study employs a Type 3 Hybrid design to simultaneously examine the implementation process and effectiveness in five NICUs. To stagger implementation across the clinical sites, we use an incomplete stepped wedge design. The five participating NICUs were purposively selected to represent different acuity levels, number of beds, locations and populations served. Our implementation strategy integrates our experience conducting H-HOPE and a well-established implementation model, the Consolidated Framework for Implementation Research (CFIR). The CFIR identifies influences (facilitators and barriers) that affect successful implementation within five domains: intervention characteristics, outer setting (the hospital and external events and stakeholders), inner setting (NICU), implementers’ individual characteristics, and the implementation process. NICUs will use the CFIR process, which includes three phases: Planning and Engaging, Executing, and Reflecting and Evaluating. Because sustaining is a critical goal of implementation, we modify the CFIR implementation process by adding a final phase of Sustaining.

**Discussion:**

This study builds on the CFIR, adding Sustaining H-HOPE to observe what happens when sites begin to maintain implementation without outside support, and extends its use to the NICU acute care setting. Our mixed methods analysis systematically identifies key facilitators and barriers of implementation success and effectiveness across the five domains of the CFIR. Long term benefits have not yet been studied but may include substantial health and developmental outcomes for infants, more optimal parent-child relationships, reduced stress and costs for families, and substantial indirect societal benefits including reduced health care and special education costs.

**Trial registration:**

ClinicalTrials.gov registration number NCT04555590, Registered on 8/19/2020.

## Background

### The high cost of preterm birth

Premature birth is associated with immaturity of major organs and regulatory behaviors, feeding difficulties, and slower early growth, leading to longer initial hospitalization and increased economic costs [1–14]. Parents of preterm infants also experience an increase in stress, anxiety, depressive symptoms, and lack of confidence about parenting, which also leads to less optimal parent-infant interaction and adversely impacts infant growth and development [15–25]. Preterm births account for only 10–12% of births in the US, but the cost of preterm birth accounts for more than 40% of the total costs of birth hospitalizations [1, 5, 7, 26–28]. Post-discharge, 19% of preterm infants experience ongoing medical conditions, increasing average outpatient costs in the first year to approximately $10,000, and prescription costs to approximately $1800 [27, 29]. The first year total health care costs for preterm infants are three times higher when compared to full-term infants, reaching $14 billion in 2017 [30]. For very preterm infant survivors (28–31 weeks gestation), and extremely preterm infant survivors (< 28 weeks gestation), these medical costs are even higher.

Early developmental interventions have the potential to improve outcomes for preterm infants and families. Importantly, early investment in preterm infant development has high potential impact on infant short and long term outcomes, parent-infant relationships and public health and education costs [5, 7, 27, 31]. The Physical Environment Exploratory Group endorses use of sensory interventions, including massage, as standard care after 30–31 weeks post-menstrual age (PMA, calculated as gestational age at birth plus chronological age) [32]. A large body of evidence supports that these interventions accelerate early brain development and maturation of visual function, improve feeding ability and growth factors, as well as health, long-term language, motor, and cognitive development. For the parents, the interventions increase interactive engagement with their infants and parent-infant interaction, which may mitigate the effects of increased parental stress [18, 32–48]. Multi-sensory developmental interventions that have a behavioral focus have been found especially effective in accelerating feeding, growth, and development [32, 33, 43, 49, 50]. However, few neonatal intensive care units (NICUs) provide evidence-based standardized parent directed early developmental interventions that have a behavioral focus as routine care. Lack of implementation is a major gap between research and clinical practice.

H-HOPE is a standardized intervention ready for dissemination. Our team developed the H-HOPE intervention (Hospital to Home: Optimizing the Preterm Infant’s Environment) to promote early infant development and parental engagement. H-HOPE consists of two components, one infant-directed and one parent-directed. Together, these components simultaneously address the needs of both preterm infants and their parents, especially their need for mutual engagement in NICUs. Our early research documented the efficacy of H-HOPE’s infant-directed component, the ATVV, which provides **A**uditory (voice), **T**actile (moderate touch massage), **V**isual (eye to eye), and **V**estibular (rocking) stimulation. We renamed the ATVV as Massage+ to be more readily understood by parents. Massage+ is initiated when infants are ready for social interaction around 31–32 weeks. When tested with infants at varying degrees of risk, Massage+ improved infant oral feeding and social interactive skills prior to and during feeding, improved their capacity to attain alert behavioral states more optimal for feeding and parent-infant interaction, in-hospital growth (weight gain) and development, and reduced length of hospital stay [11–14, 51–55]. However, Massage+ alone did not address parents’ reported distress and their need for participatory guidance and social support to engage with their infants, despite the infants’ immature behaviors. To meet parents’ needs, we developed the parent-directed component of H-HOPE, which consists of 4 participatory guidance sessions for parents, 2 during the NICU stay and 2 during the transition to home.

Together, H-HOPE’s components optimize early infant behavior and parental capacity to engage in social interaction. In previous research, we found improved developmental maturation (more mature behavioral states, increased frequency of orally directed behaviors, faster transition from gavage to oral feeding, improved sucking organization and motor development), greater in-hospital growth (weight gain and length), and enhanced engagement, social interaction and infant responsivity [43, 49, 50, 56]. Additionally, H-HOPE reduced initial in-hospital costs (net savings of $13,976 per infant after adjusting for the mean intervention cost of $680) [57] and health care use from discharge through 6-weeks corrected age (CA, chronological age corrected for weeks born preterm) [58]. With established efficacy and a manualized standardized protocol, H-HOPE is ready for widespread implementation, making H-HOPE uniquely suited as an early behavioral intervention for preterm infants in NICUs.

### Preparing NICUs to adapt H-HOPE as the standard of care

To reduce the gap between research and implementation, clinicians need a strategy to introduce an early behavioral intervention involving parents within the high-acuity NICU. Our implementation strategy integrates our experience conducting H-HOPE and a well-established implementation model, the Consolidated Framework for Implementation Research (CFIR) [59]. The CFIR identifies influences (facilitators and barriers) that affect successful implementation within five domains: intervention characteristics, outer setting (the hospital and external events and stakeholders), inner setting (NICU), implementers’ individual characteristics, and the implementation process. We selected the CFIR because the framework integrates the best features of previous models [59] and captures the complexity of real-world implementation to identify site-specific factors and patterns across cases [60, 61]. The framework has been used for diverse interventions in inpatient, clinic and community settings. A systematic review in 2016 identified 26 empirical studies using the CFIR, [62] and there are numerous studies published since then [43, 63–71]. However, only two previous studies occurred in a high acuity inpatient setting (adult acute care units) [63, 70] and no prior studies include the NICU setting. The CFIR provides a systematic approach that will be used to guide the process of implementing H-HOPE in NICUs, to recognize facilitators of successful implementation, and to identify and address implementation barriers across different sites. NICUs will use the CFIR process, which includes three phases: Planning and Engaging, Executing, and Reflecting and Evaluating. We modified the CFIR implementation process by adding a final phase of sustaining H-HOPE without continued support from the research team, because sustaining is a critical goal of implementation [72, 73].

In addition to adopting an implementation model, we modified the H-HOPE protocol used in the efficacy study to further facilitate implementation of H-HOPE as the standard of care for this initial study, nationwide and eventually globally. We expanded infant and parent eligibility criteria to reach a wider range of preterm infants and their parents who can benefit from an early behavioral intervention. In collaboration with Pathways.org, an organization dedicated to early childhood development, we developed a web-based support package of training webinars, Massage+ videos and downloadable materials for H-HOPE providers and trainers (www.Pathways.org). We replaced costly post-discharge home visits with screen time (e.g. FaceTime). Through regular interactive consultation at each site, the research team will share their experiences to support implementation and lessons learned across sites will be incorporated into the web-based support package. Because every NICU represents a different context, we view the implementation process as a collaboration that balances fidelity to intervention core components to maintain H-HOPE’s effectiveness, while adapting non-essential aspects (e.g. training format, who provides services) to fit each site’s unique set of needs [74, 75].

### Study aims

#### Aim 1 (implementation success)

Identify the degree of implementation success at each clinical site every 2 months from Executing through 6 months after supported implementation ends (*primary implementation outcome)*. Success measures include: Sustainability (offering H-HOPE), Reach (% of eligible parent-infant units receiving H-HOPE) and Degree of Implementation (mean H-HOPE services received).

#### Aim 2 (effectiveness)

Evaluate the effectiveness of H-HOPE compared to a pre-H-HOPE comparison cohort. We hypothesize that the H-HOPE cohort will have:

H2a. More positive infant outcomes including improved growth in the NICU and fewer illness visits from initial discharge through 6-weeks post discharge *(primary H-HOPE effectiveness outcomes)*.

H2b. Lower initial hospitalization costs from entry into H-HOPE through discharge, taking into account the implementation costs of the H-HOPE program per infant, resulting in long-term hospital/health system cost savings *(secondary H-HOPE effectiveness outcome).*

H2c. More positive parent outcomes, including increased visits in the NICU, lower NICU- related worry, lower anxiety and depression, and greater confidence in premature infant care *(exploratory H-HOPE effectiveness outcomes)*.

#### Aim 3 (influences associated with success and effectiveness)

Determine the influences of the 5 CFIR domains associated with success (Aim 1) and the primary H-HOPE effectiveness infant outcomes (Aim 2).

## Methods/design

The study employs a Type 3 Hybrid design [76] to simultaneously examine the implementation process and effectiveness in five NICUs. To stagger implementation across the clinical sites, we use an incomplete stepped wedge design [77] (see Fig. 1). This design is more advantageous than conventional cluster randomized trials because it requires fewer NICUs (clusters), allows all NICUs to implement H-HOPE, and permits an estimate of treatment effects both within- and between-NICUs [77–80]. To eliminate systematic bias due to order of initiation, start dates were determined by a random number generator. Each NICU implements H-HOPE in 3 phases: Planning and Engaging (6 months), Executing (6 months), and Reflecting and Evaluating (2 months) [81, 82]. Implementation is followed by 6 months of Sustaining.

**Fig. 1 Fig1:**
[figure not shown]
Incomplete Stepped Wedge Design. Pre-I & P = 6 months of pre-implementation plus Planning and Engaging during which Pre-H-HOPE Comparison Cohort Data are collected simultaneously, E = 6 months of Executing at the end of which posttest will be taken, R = 2 months of Reflecting and Evaluating, S = 6 months of Sustaining. The order of implementation was randomly assigned

To evaluate effectiveness, we chose not to use a randomized design with simultaneous intervention and control comparison groups because it would be confusing for nursery staff and parents to have two different standards of care. Because this is an implementation study, H-HOPE will be introduced as the standard of care. All eligible infants will receive H-HOPE whether or not their parents enroll in the research study. Instead, we compare parent and infant outcomes before and after the introduction of H-HOPE at each site.

### Study setting and sample

To maximize generalizability of results, we selected 5 NICUs that are diverse in size (26–72 beds), acuity level (one level II, two level III, and two level IV NICUs), location (urban/suburban/rural), and population served (See Table 1). All participants will give written informed consent. Our study population is anticipated to include 44% White, 26.6% Black/African American, 0.6% Native American, 6% Asian, 19% Latinx, and 3.7% other. These estimates include substantially fewer Latinx, a group with the lowest prematurity rate of 9.9%, and larger proportion of Blacks and Native Americans, the groups with the highest prematurity rates in the US (Blacks, 13.8%; Native Americans, 11.4%) [83]. All of the NICUs provide developmental care that includes non-disruption of sleep cycles and skin-to-skin care when infants are stable. Comparisons across units will help identify NICU characteristics that make it more challenging to implement and sustain H-Hope. Sites 2 and 3 are in the same health system. Therefore, these NICUs will implement H-HOPE simultaneously and are considered as one site for effectiveness evaluation (Aim 2). However, they will be analyzed as separate sites for success and influences (Aims 1 and 3) because the inner settings differ, e.g., they have different nursing staff and hospital administrators.

**Table 1 Tab1:** Expected H-HOPE Cohort and Site Characteristics

NICU Site^a^	NICU Level	Annual Admissions^b^	# Eligible in 6 Months^c^	# Enrolled^c^	# Retained^c^	Race/ethnicity^d^%					% Medicaid	Location
						Wh	Blk	Am Ind	Asian	Latinx		
Site 1	III/IV	184	62	44	31	16	71.2	0	0	12.8	74.5	Urban
Sites 2 and 3	III/IV, II	454 119	222 30	155 21	108 15	38	48	8	2	4	70	Rural/ Suburban
Site 4	III	297	148	111	77	62.8	6	0	15.5	14.9	40	Suburban
Site 5	III	150	69	48	34	89	1.8	3	2.2	4	36	Rural
TOTAL(s)		1205	542	379	265	42.7	34.9	4.5	4.8	7		

^a^In order of Random Assignment; ^b^Annual Admissions for 23–35 wk. GA; ^c^# eligible, # enrolled is at a 70% enrollment rate & # retained at 6-weeks post discharge for H-HOPE Cohort; ^d^White, Black/African American, American Indian, Asian, Latinx

### Sample

Aim 1 (Implementation success) data will be obtained from each site’s de-identified aggregated electronic health record (EHR) data.

Aim 2 (Effectiveness) participants include both parents and infants from two cohorts of subjects: the Pre-H-HOPE Comparison Cohort and the H-HOPE Cohort. The Pre-H-HOPE Comparison Cohort consists of two sub-cohorts: 1) Consented Pre-H-HOPE Parent-Infant Units, for whom all parent and infant data are collected and 2) Non-Consented Pre-H-HOPE Infants for whom only de-identified existing infant growth and cost data are used. The non-consented Pre-HOPE Cohort is added to have a large enough sample for propensity score matching to test H-HOPE’s impact on infant growth and initial hospitalization costs.

#### Eligibility criteria and recruitment

For H-HOPE and Pre-H-HOPE Consented parent-infant dyads, infants are eligible if they are born at 23–35 weeks gestational age, at least 31–32 weeks PMA, and clinically stable. Parents are mothers, fathers, or other significant family member who intend to act in the role of a parent, regardless of biological relationship to the infant, gender identity or sexual orientation. In most cases the biological mother is identified as the primary parent and she will be asked to name the second parent. The Non-Consented Pre-H-HOPE Infants must meet the same infant criteria, however no parents are involved.

#### Sample size and power for aim 2 effectiveness

Based on participating sites’ data, 542 infants will be eligible for the H-HOPE cohort during the 6-month Executing phase. Of the available infants, we expect to enroll at least 70% (*n* = 379 parent-infant pairs) and to retain 265 through 6-weeks following the infant’s discharge. During a 12-month period before H-HOPE implementation, 1084 eligible infants will be available for the Pre-H-HOPE Comparison Cohort in two sub-cohorts.

The first sub-cohort, the Consented Pre-H-HOPE Parent-Infant Units, is recruited at the same time as the Planning and Engaging phase at each site and will contribute to all outcome analyses (*n* = 542). The retention rates will be the same in the Consented Pre-H-HOPE sub-cohort and the H-HOPE cohort (*n* = 265). The second sub-cohort, the Non-Consented Pre-H-HOPE Infants (*n* = 542), will contribute only retrospective infant growth and cost data obtained from de-identified EHR and cost records in the 6 months prior to the start of Planning and Engaging. Based on our prior research, near medium to large effect sizes are expected for the primary outcomes of infant growth and health care utilization following discharge [49, 57] and the secondary hospital cost outcome [58]. Using the STATA package *stepped wedge* [84], the power analysis found that there will be at least 80% of power to detect a medium effect of Cohen’s *d* = − 0.50 at a significance level of α = .05 in this stepped wedge design with 4 sites and an average of at least 50 subjects per site (or 200 in total) across 4 staggered time points, assuming the intra-class correlation coefficient (ICC) is .1, a common ICC found in health and behavioral research [85, 86]. Assuming ICC as .05, which is common ICC health cost analysis [87–89], research would require at least 30 subjects per site (or 120 in total). Thus, in this proposed study, the anticipated total sample size of 265 will be adequate to detect a medium effect for all outcome measures.

The Aim 3 sample includes hospital personnel and parents receiving H-HOPE at each site. Consented H-HOPE parents will be randomly selected (15 parents per site, 75 total) to be interviewed prior to discharge and when their infant is 6-weeks post discharge. Purposively selected hospital personnel include at least one hospital administrator, NICU leadership (e.g. medical director and nurse manager), clinical site H-HOPE team members (2–4 per site), and selected staff who work in the NICU (10 per site) who have delivered H-HOPE, especially champions and non-supporters. Each of these selected hospital personnel will participate in 3 short qualitative interviews about their experience with H-HOPE. In addition, all registered staff nurses who work at least 50% in the NICU will complete a brief survey regarding engagement and burnout during the three project phases.

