#### Aim 2 analysis

Aim 2 evaluates the effectiveness of H-HOPE including infant growth, health care utilization following discharge, infant hospital costs. Aim 2 also explores the impact of H-HOPE on parent outcomes detailed in Table 2*(exploratory outcomes)*. The Quantitative Data Center analyzes Aim 2 measures.

Before analytic modeling, propensity score methods [101–104] will be utilized to reduce any selection bias by ensuring balanced distributions of infant and primary parent characteristics between Pre-H-HOPE and H-HOPE infants. For the growth and infant hospital costs outcomes, propensity scores will first be computed using available infant and parent characteristics. Then, pairs of infants will be created by matching each infant in the H-HOPE cohort with an infant in the pre-H-HOPE cohort with the same or most similar propensity scores. The final analytical models will be applied directly to propensity-score-matched pairs.

For the other Aim 2 outcomes, including health care utilization from discharge through 6-weeks post discharge and the exploratory parent outcomes, data are collected directly from parents and are not available in hospital records. Therefore, propensity score weighting will be used. In propensity score weighting, propensity scores will first be computed similarly to propensity score matching. Then propensity scores will be used to calculate inverse probability of treatment weights as weighting scores, rather than matching samples (i.e., infants or parents). The propensity weighting scores will be incorporated in weighted final analytical models preserving the entire sample for final analytical modeling.

In all the final analytical modeling, linear mixed models will be utilized to analyze normally distributed outcomes [80, 105] (e.g., infant growth and parent outcomes). Linear mixed models are an extension of linear regression models to allow estimating both between-site and within-site effects when there is a nested data structure (e.g., individual patients/infants are nested within sites). Generalized linear mixed models, an extension of linear mixed models, will be used to analyze non-normally distributed outcome measures (e.g., infant health care utilization, hospital costs).

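### The 80% power for Aim 2 treats the ICC as known; once the site variance is estimated from 4 sites, 80% power and a 5% error rate do not hold together for the parent-reported outcomes in the layout that reproduces the figure

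*Protocol article*

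**What the plan says.** The section on sample size and power for Aim 2 puts the power for a Cohen's d of -0.50 at 80% or more, with alpha set to .05. The setting behind that figure is "in this stepped wedge design with 4 sites and an average of at least 50 subjects per site", and the ICC is taken to be .1. At an ICC of .05 the section asks for 30 per site. It concludes that the anticipated 265 "will be adequate to detect a medium effect for all outcome measures".

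There are 4 sites, not 5, because the section on study setting and sample merges Sites 2 and 3 for Aim 2. The Methods/design section says that the stepped wedge "permits an estimate of treatment effects both within- and between-NICUs". The Aim 2 analysis section says that "linear mixed models will be utilized to analyze normally distributed outcomes", with infants nested in sites, and that generalized linear mixed models handle the other outcomes. It names no reference distribution and no period term.

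The sample sections also define a second, non-consented pre cohort from the 6 months before Planning and Engaging. It contributes growth and cost data only.

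**The concern.** The standard stepped-wedge power formula fixes the between-site variance at the assumed ICC and uses a normal cutoff. The planned analysis has to estimate that variance. With 4 sites the estimate is poor, and how much this matters depends on how far the treatment estimate relies on comparisons between sites. If it relies on them heavily, an ordinary z test rejects too often, and a test that keeps close to 5% loses power. The stated power, the stated alpha and the closing claim about 265 would then not hold together for at least some outcomes. One of these, acute care visits, is a primary effectiveness outcome.

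**Working it through.** **Inputs.** From the power section: d = 0.50, alpha .05 (taken as two-sided; not stated), 4 sites, 50 per site at ICC .10, 30 per site at ICC .05. From Table 1, retained by Aim 2 site: 31, 108 + 15 = 123, 77, 34 (sum 265), applied to each cohort because the power section gives 265 for both. Assumed: total variance 1; 50 or 30 means per site *per cohort* (the favourable reading); one pre and one post window per site; starts one window apart; categorical periods.

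**Step 1: reproduce the stated figures.** The layout has 8 cells over 5 periods. The first and last periods hold one cell each, which its own period effect absorbs. Each middle period holds one site in post and the next site in pre. Their difference is the treatment effect plus a difference of two site effects plus sampling error. With site variance τ² = ICC and σ² = 1 − ICC, each of the three differences has variance a = 2τ² + 2σ²/n, and neighbours have covariance b = −τ². Generalised least squares gives

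Var = (a² − 2b²) / (3a − 4b), power = Φ(0.5/SE − 1.96).

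- ICC .10, n = 50: a = 0.200 + 0.036 = 0.236, b = −0.1. Var = 0.035696/1.108 = 0.0322, SE = 0.1795, power = Φ(0.826) = 79.6%.
- ICC .05, n = 30: a = 0.1000 + 0.0633 = 0.1633, b = −0.05. Var = 0.021678/0.690 = 0.0314, SE = 0.1772, power = Φ(0.861) = 80.5%.

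Other layouts miss at ICC .10: 50 per site split over pre and post, 66.0%; complete 4 × 5 design with 10 per cell, 57.2%, or 50 per cell, 99.6%; no period effects, about 100%.

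**Step 2: where the information comes from.** Each site's before-after difference is the treatment effect plus one period change. That gives 4 equations in 5 unknowns. The site-plus-period design matrix has rank 8 with or without the treatment column. So within sites the effect is not identified, and the estimate rests on the three between-site differences. After the effect is fitted, two contrasts remain to inform the site variance. More infants help little at ICC .10: as n grows, Var tends to (0.04 − 0.02)/(0.6 + 0.4) = 0.02, so SE cannot fall below 0.141, against 0.172 at the Table 1 sizes.

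**Step 3: estimate the site variance.** Simulation of this layout, Gaussian outcome, REML site variance, residual variance known. Power is given first for a Satterthwaite t test, then for a cutoff calibrated to exactly 5%.

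| Setting | Known-ICC formula | Wald z type I error | Power |
|---|---|---|---|
| ICC .10, 50 per site per cohort | 79.6% | about 10% | 58% to 66% |
| ICC .10, Table 1 sizes | 82.6% | about 11% | 58% to 66-71% |
| ICC .05, 30 per site per cohort | 80.5% | about 7% | 69% to 75-76% |
| ICC .05, Table 1 sizes | 94.0% | about 9% | 77% to 86-88% |

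Satterthwaite error is about 6.5-7% at ICC .10 and 5-6% at ICC .05. The calibrated cutoff is a benchmark, since setting it requires the true ICC.

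**Step 4: growth and cost.** These have two pre windows, so 12 cells. Site plus period effects have rank 9, and 10 with treatment, so the effect is estimable within sites. With matched pre infants spread over both windows at ICC .10, size-calibrated power is about 72-75% with 265 pairs and 83-88% with 379. The random-intercept z error is still about 10%, and Satterthwaite error about 8-9%. A fixed-site analysis, which estimates no site variance, has about 68% power with 265 pairs and 83% with 379 (44, 176, 111 and 48 by site); the latter is 81% at ICC .05.

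**Step 5: other staggers.** Starts 2 to 4 months apart give about 80-87% power at the Table 1 sizes, with z error still 6-9%. With no period term, formula power exceeds 98%, but the comparison is then a plain before-after one.

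**The case against.** A reader might infer that Aim 2 as a whole has 58% power and a doubled error rate. The documents do not support that, for four reasons, each of which stands in part.

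- **Growth and cost are different.** The non-consented pre cohort exists for exactly these outcomes. Growth is measured at discharge, so the 379 enrolled are more relevant than the 265 retained at 6 weeks, and with 379 pairs power reaches 80%. The power shortfall therefore falls mainly on acute care visits and the parent measures. What remains for growth and cost is the error rate of a default random-intercept test.
- **The stagger is unseen.** The one-window layout is inferred. That one layout returns both stated figures is good evidence for it, but not proof of what Fig. 1 shows. Shorter staggers would largely restore the power.
- **58% belongs to one test.** At an exact 5% level, power with 50 per site is about 66%. For acute care visits the plan is a generalized model, so results from a Gaussian simulation are approximate.
- **The test is not named.** Nothing says that a Wald z test will be used, and a degrees-of-freedom correction could sit in an analysis plan that is not shown. This answers the error-rate half taken alone. It does not rescue the power section: a correction that restores 5% lowers the power below the figure printed there.

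**Conclusion.** The point holds in a limited form. The stated 80% reproduces only by treating the ICC as known, in a layout where the treatment effect is recovered between sites, while the planned model must estimate the site variance from 4 sites. For outcomes with only the consented pre cohort, power at ICC .10 is some 14 to 22 points below the stated 80% at 50 per site per cohort (80 − 66 and 80 − 58). At the Table 1 sizes it is 9 to 22 points below (80 − 71 and 80 − 58). At ICC .05 the Table 1 sizes give 77-88%, close to or above 80%, so the shortfall there is small or absent. The claim that 265 is adequate for every outcome measure is not supported at ICC .10. The claim of a within-NICU estimate fails for these outcomes in this layout but holds for growth and cost.

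This rests on the inferred stagger, categorical periods, a Gaussian outcome and the per-cohort reading of the sample sizes. It should be corrected; it does not invalidate the design.

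**What to change.** 1. In the power section, restate power separately for growth and cost and for the parent-reported outcomes. Use the true Fig. 1 stagger, a test valid for 4 sites, and a site variance that is estimated.
2. Replace the statement that 265 is adequate for all outcome measures with that restated power, or with the detectable effect.
3. In the Aim 2 analysis section, name a small-sample method and check its 5% size by simulation: for example Kenward-Roger or Satterthwaite for the linear models, and a permutation or bias-corrected equivalent for the generalized ones. The simulation check matters because Satterthwaite alone ran at about 8-9% for growth and cost. For those two outcomes, a fixed-site analysis is an alternative that needs no between-site variance.

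The cost is wording in the power paragraph, one analysis specification and a short simulation. No extra infants or data are needed. The price is a less favourable stated power and wider confidence intervals.
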